## 18.4 Actions to be Undertaken

The PI is responsible for the appropriate medical management of all AEs and for the personal safety and well-being of participants. In case of an AE, the PI will initiate appropriate treatment according to his/her medical judgment and will decide whether to withdraw the participant from the study.

## 18.5 AE Collection Period and Follow up

All AEs and SAEs will be monitored continuously during the study from the time of signing the ICF until the End of Study. SAEs will be followed until resolution, including post Day 365/End of Study if warranted.

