After day 42, all participants will be given follow-up visits at Norra Stockholms Psykiatri for up to one year after dosing, to study dedicated physicians or nurses at a frequency determined by the health care professional. If needed to reach/stay in remission, the participants will be provided antidepressant treatment in accordance with the regional guidelines for antidepressant treatment ([https://psykiatristod.se/regionala-wardprogram/depression](https://psykiatristod.se/regionala-vardprogram/depression)). At least monthly the participants will be asked to provide on-line symptom rating data (via 1177.se). At the 365-day visit, symptoms will be evaluated using MADRS, CGI-I and CGI-S. After completing the study (one year or withdrawal), participants will be subject to standard care, including referral in accordance with regional guidelines.

The study outcome measures will be used to assess depressive symptoms, clinical global functioning, functional disability, anxiety symptoms and health-related quality of life. Safety outcome measures will be collected at all assessment time points from the time of consent through the end of study.

To enhance participant safety, the current study proposes to test psilocybin within a “set and setting” (SaS) protocol similar to the protocol that has been used in all modern studies of psilocybin in both diseased and normal healthy populations. The SaS protocol for this study includes: 1) a preparation with session Facilitators (licensed psychologists) prior to dosing; 2) administration of study medications in an aesthetically neutral room under the supervision of two Facilitators who are present throughout the session (with the exception of short, temporary allowances for facilitator breaks; e.g. bathroom breaks); and 3) three post-dose integration sessions during which participants are encouraged to discuss their intervention experience with the Facilitators. To evaluate the Facilitators' adherence to the study manual, and the role of Facilitators' and participants' in-session behaviors for treatment outcome, all five sessions in the trial with Facilitators present will be recorded. The SaS will be identical for those randomized to psilocybin or niacin active placebo.

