### Unsolicited Adverse Events

Any other observed and participant reported AEs and SAEs will be recorded throughout the study, following written informed consent. SAEs will be reported in accordance with the medical Product Agency (MPA) guidelines.

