## 5.4 Safety Objectives

The overall safety objective of this study is to evaluate a single 25 mg oral dose of psilocybin compared to an active placebo in incidence, severity and frequency of Adverse Events (AEs), Treatment Emergent AEs (TEAEs), Solicited AEs, and Serious Adverse Events (SAEs) before, during and after the dosing session and at all follow-up visits.

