| MLQ & SWLS (SRP)           | 1          | MD1    |        |          |          |          |         |          |          |          |          |          | MD1       |
| LEQ (SRP)                  | 3          | MD1    |        |          |          |          |         |          |          |          |          |          | MD1       |
| CGI-S                      | 1          | MD1    |        |          |          |          |         |          |          |          |          |          | MD1       |
| CGI-I                      | 1          | MD1    |        |          |          |          |         |          |          |          |          |          | MD1       |
| Adverse event interview    | 3          | X      |        |          |          |          |         |          |          |          |          |          |           |
| Total duration/day (min)   |            | 26     | 6      | 6        | 6        | 6        | 6       | 6        | 6        | 6        | 6        | 6        | 23        |
| Visit at research site (v) |            | V      |        |          |          |          |         |          |          |          |          |          | V         |

Dur = approximate duration for patient (minutes), W-S = Web screen, S-Day = Screening day, MD1 = Study physician, Medical doctor and study coordinator, MD2=Medical Doctor at MHS, MDs = Screening responsible MD, MD-M = [name]\_P = PET responsible MD, MHS = Mottagningen för hjärnstimulering, MHS\_N = Dedicated nurse from MHS, SRP = Self rating by patient, SRF = Self rated by facilitator, TC = TakeCare, BP = Blood pressure, HR = Heart rate, T-Exp = Treatment Expectation, T-Eval = Treatment Evaluation, PDRF = Post dose release form, PDM = Post dose monitoring, BSB = Blood sampling biomarkers. X = completed by patient. PET2 is done day on 15±7.after LP2 and PET2

Table 1: Schedule of assessments

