### **9.11 Early Termination Visit**

Should a participant terminate early, including Prep Phase Terminations and participants who are randomized and later terminate or are terminated for safety reasons, the End of Study visit (day 365) assessments will be completed to the extent possible within 14 days. The End of Study Plan will be discussed at the termination/End of Study visit. An End of Study visit will not be conducted for Screen Failures.

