#### **16.4.6 Safety Analyses**

All recorded AEs will be coded using MedDRA and presented by SOC and preferred term with number of subjects, percentages and number of events overall and by study period. The worst severity will be used for each event. TEAEs, solicited AEs, SAEs and AEs related to treatment will be summarized similarly. AEs leading to discontinuation from the study will be listed and tabulated.

All concomitant medications will be listed. Safety data collected for the period from Screening through the Baseline assessment and during the Preparation Phase will be presented separately from post-dose safety data (treatment emergent).

All solicited AEs observed in randomized participants who received psilocybin or niacin placebo will be reported.

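### Table 1 schedules no adverse event interview at the pre-dose procedure visits or after Day 42, including Day 365, although the text promises collection from consent to end of study

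*Protocol*

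**What the plan says.** The text of the protocol makes a broad promise in several places.

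- Section 18.5: "All AEs and SAEs will be monitored continuously during the study from the time of signing the ICF until the End of Study".
- Synopsis, Study Description and Overview, repeated in section 6.1: "Safety outcome measures will be collected at all assessment time points from the time of consent through the end of study".
- Section 5.4 sets the safety objective as a comparison of AE incidence, severity and frequency "before, during and after the dosing session and at all follow-up visits". SAP section 2.4 repeats it.
- Synopsis, Unsolicited Adverse Events: "Any other observed and participant reported AEs and SAEs will be recorded throughout the study, following written informed consent".
- Section 16.4.6 expects pre-dose safety data to exist: "Safety data collected for the period from Screening through the Baseline assessment and during the Preparation Phase will be presented separately".

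The schedule is narrower. In Table 1 (section 6.3) the row "Adverse event interview", with a duration of 3 minutes, is marked at Days 0, 1, 8 and 15 in the first part and at Day 42 in the second. It is blank at screening, MRI1, the first lumbar puncture (LP1), PET1, Day -1, every monthly point and the in-person Day 365 visit. Section 9.8 lists only rating scales for the end-of-study visit.

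For early termination, section 9.11 says that "the End of Study visit (day 365) assessments will be completed to the extent possible within 14 days". This covers participants who leave in the preparation phase as well as randomized participants who stop later.

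**The concern.** The safety endpoints in section 5.4.2 compare AE incidence between arms with no Day 42 limit, so a one-year AE table is to be expected. Up to Day 42 every participant is asked in the same way on the same days. After Day 42 the schedule contains no general AE enquiry, even when the participant is in the clinic at Day 365.

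What is left after Day 42 is spontaneous report and whatever is noted at clinic visits whose frequency, according to the synopsis, the health care professional decides. If one arm needs more care in that period, it will be seen more often and more of its events may be recorded. The comparison would then partly reflect how often people were seen.

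Section 17.1.2 gives a reason to ask late: it describes visual disturbances after serotonergic hallucinogens that can persist from weeks to years, although it adds that none has occurred in contemporary psilocybin research.

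There is also a smaller group with no scheduled enquiry at all: participants who undergo LP1, or PET1 with its arterial line, and then leave before dosing.

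**Working it through.** **Step 1. Are the blank cells real?** Tables read from PDF can lose marks, so I added the row durations in each Table 1 column and compared them with the printed total per day. In the first part the empty Day -2 total has dropped out, so from Day -1 onward the printed totals sit one column to the left. I read them with that shift.

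| Column | Rows other than AE (min) | AE interview | Sum | Printed |
|---|---|---|---|---|
| MRI1 | 60+1 = 61 | 0 | 61 | 61 |
| Day -10 (LP1) | 60 | 0 | 60 | 60 |
| Day -3 (PET1) | 10+5+5+120+3+1+1+1 = 146 | 0 | 146 | 146 |
| Day -1 | 5+60+2+2+1+1+3 = 74 | 0 | 74 | 74 |
| Day 1 | 90+3+60+1 = 154 | 3 | 157 | 157 |
| Day 8 | 87 | 3 | 90 | 90 |
| Day 15 | 274 | 3 | 277 | 277 |
| Day 42 | 10+3+1+1+1+1+1+3+1+1 = 23 | 3 | 26 | 26 |
| Each monthly point | 3+1+1+1 = 6 | 0 | 6 | 6 |
| Day 365 | 10+3+1+1+1+1+1+3+1+1 = 23 | 0 | 23 | 23 |

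The web screen (13), screening day (145) and Days 2-7 (3) also reproduce without an AE interview. Day 0 was not summed, because its printed 480 minutes is the dosing session alone. Day 42 and Day 365 carry the same rows apart from the AE interview, and their totals differ by 26 - 23 = 3 minutes, exactly its length. The omission is in the schedule itself.

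**Step 2. Size of the gap after dosing.** The last scheduled interview is Day 42, so 365 - 42 = 323 days follow it, and 323/365 = 0.885, or 88% of the post-dose period.

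**Step 3. The pre-dose procedures, dosed participants.** PET1 takes place 1 to 7 days before dosing (section 8.5.4). On Day 0 staff ask about changes in health before dosing (section 9.3.1), and Table 1 has an AE interview that day. Events after MRI1, LP1 and PET1 can be picked up then. MRI2 is followed by the Day 1 and later interviews, and LP2 and PET2 by the Day 15 interview, the Day 42 interview, or both.

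**Step 4. The pre-dose procedures, participants who stop before dosing.** They never reach Day 0. Their termination visit uses the Day 365 set (sections 9.11 and 10.4), which has no AE interview, so the number of scheduled AE interviews is zero. Section 10.4 places them in the safety analysis set, whereas section 16.2 limits that set to participants who received treatment. Under either definition, section 16.4.6 plans to present pre-dose safety data.

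**Step 5. What one event is worth.** With 15 per arm, one participant with an event missed or found changes that arm's incidence by 1/15 = 6.7 percentage points. The documents give no figure for late AE rates or for visit frequency by arm, so the actual bias cannot be calculated.

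**The case against.** The strongest reply is that Table 1 is not the whole protocol. The text requires several things that the table does not show, such as the Day 0 urine tests (section 9.3.1), pregnancy tests on Days 8 and 42 (section 22.3) and the follow-up clinic visits of phase B. Section 18.5 is itself a requirement, and the synopsis has observed and reported events recorded throughout. Section 8 demands adherence to the schedule but does not say that nothing beyond it is done. Suicidality is followed through MADRS for the whole study (section 18.1.3). The drug is given once, so early interviews cover the time of greatest interest, and a visual effect that begins early and persists is open to detection on Days 8, 15 and 42.

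Much of this stands, and it rules out three stronger readings that a reader might infer:

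- **Harms of the study procedures go unasked.** For dosed participants they do not (step 3 of the working).
- **Follow-up after Day 42 is only on-line, or only what patients volunteer.** The synopsis provides visits to study physicians or nurses alongside the monthly on-line ratings, and observed events count.
- **88% of the safety information is lost.** The figure counts calendar days without a scheduled interview. It is not a share of events, and the risk from a single dose is not spread evenly over the year.

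The reply does not remove the mismatch. Permission to record an event is not a scheduled enquiry. The phase B visits have no fixed frequency and no scripted AE question, and the text promises collection at all assessment points and all follow-up visits.

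**Conclusion.** The point holds in a limited form. The text promises AE collection from consent to the end of the study and at every assessment point or follow-up visit. Table 1 provides a scheduled AE interview on five days, Day 0 to Day 42. None is scheduled for the remaining 323 post-dose days, and none at Day 365.

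One-year AE incidence would therefore combine systematic enquiry up to Day 42 with unsystematic capture afterwards. That the later part may differ between arms is an inference from the discretionary visit frequency; the documents do not show that it will. SAP section 5.7 plans counts and percentages without tests, so the effect falls on the reported incidence and its reading.

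The pre-dose gap matters mainly for participants who stop before dosing, who have no scheduled AE interview. The documents do not say how many these will be. This is an inexpensive improvement to the schedule, and it does not bear on the primary efficacy analysis.

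**What to change.** Add the existing AE interview to Table 1 at Day 365. The visit total goes from 23 to 23 + 3 = 26 minutes, the same as Day 42. Because early termination uses the Day 365 assessments, the same mark gives an AE interview to participants who leave early, including those who leave in the preparation phase. State this in sections 9.8 and 9.11.

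Optionally add it at Day -1, where the total goes from 74 to 74 + 3 = 77 minutes, so that LP1 and PET1 events are asked about before the dosing day.

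Then reconcile Table 1 with the synopsis overview and sections 5.4, 6.1 and 18.5, so that the wording matches what is scheduled. If events between Day 43 and Day 365 continue to be collected only by spontaneous or incidental report between visits, say so wherever one-year AE incidence is reported.

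The cost is about 3 minutes at existing visits and a small amendment to the table. Two larger changes are not needed. An AE question in the monthly on-line form would require someone to review the entries, given the 24-hour SAE reporting in section 18.6. Restricting the safety objective to Day 0-42 would conflict with section 18.5 and with the synopsis text on unsolicited events.

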## 18.6 Regulatory Reporting

All SAEs will be reported by PI or designee, whether or not considered causally related to psilocybin, placebo or to the radioligand/ study procedure(s). SAEs will be collected in a list, which will be sent to the Swedish Medical Products Agency (MPA) and the IRB once a year until the study is on-going. In the case of a SAE, an assessment of the security of the subjects participating in the study will also be included. For fatal or life-threatening AEs where important or relevant information is missing, active follow-up will be undertaken immediately by the investigator by interview and/or physical examination and follow-up as deemed necessary by the investigator. In order to enable specific treatment of drug related AEs unblinding will be possible via the investigator (24 hrs phone accessibility). Unblinding will be only performed if it is necessary for the investigator to have this knowledge when making a decision on how to treat an AE. In case the knowledge will not affect treatment choice the blind will not be opened.

The following information is mandatory for the initial report:

- Subject study ID
- Study treatment
- Start date (time, if relevant) of the study treatment
- Brief description of the event (diagnosis)
- Start date (time, if relevant) of the event
- Seriousness criteria
- Causality assessment

The investigator has to inform sponsor of all SAEs within 24 hours of the investigator's awareness using a Safety-approved report form (e.g., specified SAE form or local regulatory form) and perform follow-up activities. These will include interview and physical examinations as deemed relevant and continue as long as is deemed clinically relevant by the investigator.

SLSO is responsible for the recording and reporting of any suspected unexpected serious adverse reactions (SUSARs) to the regional ethics committee and to the Eudravigilance system, clinical trials module. Life-threatening or fatal SUSARs will be reported as soon as possible but at latest within 7 days after the sponsor has become aware of it. Relevant follow-up information will be reported within 8 additional days. Other SUSARs will be reported as soon as possible but at latest within 15 days after the sponsor has become aware of it.

#### **18.6.1 Definition of reason to stop the trial**

In case of an imminent risk for any of the study participants as defined by the investigator, the trial will be stopped until the risk has been identified and corrected. The trial will not start before approval from MPA. Patients suffering from any such risk shall be given medical care as needed within Stockholm County.

#### **18.6.2 End of Trial Notification**

A final report and end of trial notification shall be reported to LMV within 90 days as required by LVFS 2011;19, 9 kap.

## **19. STUDY MONITORING, AUDITING AND DOCUMENTATION**

The PI and the study team will be trained prior to the start of the study. The study sites will be monitored on site. The site will be monitored as appropriate for the rate of enrollment in order to comply with GCP guidelines and to ensure validity of the study data. During each monitoring visit, consent forms will be reviewed, and source data verification will be performed to ensure compliance, including accurate and complete recording of data on CRFs, Source Records, and drug accountability records.

During or after the study, the regulatory authorities, the IRB, and/or representatives of the Sponsor may request access to all source documents, CRFs, and other protocol documentation for on-site audit or inspection.

All activities and responsibilities related to monitoring will be outlined in the study Monitoring Plan.

## **20. HUMAN SUBJECTS PROTECTIONS**

### **20.1 Study Conduct**

This study will be conducted in accordance with the protocol and with the following:

- Consensus ethical principles derived from international guidelines including the Declaration of Helsinki and Council for International Organizations of Medical Sciences (CIOMS) International Ethical Guidelines
- Applicable ICH GCP Guidelines
- Applicable laws and regulations
- The protocol, protocol amendments, ICFs, IB, and other relevant documents (e.g., advertisements) must be submitted to the IRB by the PI and reviewed and approved by the IRB before the study is initiated.
- Any amendments to the protocol will require IRB approval before implementation of changes made to the study design, except for changes necessary to eliminate an immediate hazard to study participants.

### **20.2 Principal Investigator Responsibilities**

The PI will be responsible for the following:

- Providing written summaries of the status of the study to the IRB annually or more frequently in accordance with the requirements, policies, and procedures established by the IRB
- Notifying the IRB/ of SAEs, Unanticipated Problems or other significant safety findings as required by IRB procedures
- Providing oversight of the conduct of the study at the site and adherence to requirements of 21 CFR, ICH guidelines, the IRB, and all other applicable local regulations

### **20.3 Human Subjects Training**

All study staff, to include any individual interacting with a participant or who has access to participant data, will be required to complete mandatory human subjects training prior to interacting with study participants.

### **20.4 Voluntary Participation**

Participants will be informed, via the ICFs and the consent process, that participation is voluntary, that refusal to participate will involve no penalty or loss of benefits to which the participant would otherwise be entitled, and that the participant may discontinue participation at any time.

## 20.5 Benefits of Participation

There is no guarantee participants will receive a direct benefit from participating in this study. Study participation will include receiving a psychiatric and medical evaluation, including standard blood and urine-based safety laboratory tests. In addition, eligible participants will have a 50% chance of receiving an intervention (psilocybin) that has been reported in past studies to provide benefit for the treatment of symptoms. In addition, many individuals' depressive symptoms improve with placebo treatment.

Participants will have the chance to contribute to a scientific investigation, which may be of benefit to future patients, and may provide a sense of personal satisfaction in this regard. Benefits to others may include gaining significant knowledge regarding the potential utility of psilocybin for patients with MDD.

## 20.6 Alternatives to Participation

Potential participants may choose not to participate in this study. Individuals suffering with major depressive disorder (MDD), have at their potential disposal a wide range of treatments and/or procedures that are viable alternatives to participation in the current study. These alternatives are described in the regional medical guidelines for the treatment of MDD, available on [www.psykiatristod.se](http://www.psykiatristod.se)

## 20.7 Study and Site Closure

The Sponsor designee reserves the right to close the study site or terminate the study at any time for any reason at the sole discretion of the Sponsor.

Study sites will be closed upon study completion. A study site is considered closed when all required documents and study supplies have been collected and a study-site closure visit has been performed.

The PI may initiate study-site closure at any time, provided reasonable cause and sufficient notice is given in advance of the intended termination.

Reasons for the early closure of a study site by the Sponsor or PI may include but are not limited to:

- Failure of the PI to comply with the protocol, the requirements of the IRB or local health authorities, the Sponsor's procedures, or GCP guidelines
- Inadequate participant recruitment
- Discontinuation of further study intervention development

